**VI. Data Custody, Security, and Confidentiality Protections**

The sections below describe types of data sources and how they will be protected. For the type(s) of data you will have, put an “X” in the appropriate box to the left of the section that best describes how you will minimize the risk of a breach of confidentiality for your study. Note, as appropriate, how you will record/store data. These descriptions represent MINIMAL measures; you may add more stringent protections and other relevant information in B.

**Confidentiality: The *LOSS OR THEFT* of 1) original/duplicate version of physical data collection instruments (forms, tapes, etc) or 2) physical devices containing electronic data (i.e. laptop/mobile device, external flash drive(s), is a threat to subject confidentiality.  Risk of such a loss/theft is increased during movement/transport of data (in any format), such as in a vehicle or other move.  Be sure to train anyone (co-investigators, staff, students, etc.) who might be engaged in the oversight of data handling/storage about this problem.  Some typical risk-mitigation strategies would include:**

- **minimizing the physical movement of data and/or devices containing data**
- **encrypting electronic data (especially when stored on any mobile device, including flash memory tools, phones, tablets, etc, or when transferring across networks)**
- **making use of reliable courier services (FedEx, DHL, etc) when physical transport of bulk data forms is necessary**
- **minimizing the transfer of identifiable data in physical or electronic form (i.e. removing/separating/destroying identifiable data, when physical transfer of data is necessary)**

A. Data Storage

| 1. Hard Copies of Data Collection Forms. | |
| --- | --- |
|  | This activity will not involve receiving and/or accessing hard copies of data |
|  | Data collection forms RECORD NO PERSONAL IDENTIFIERS connecting study participants, and there are no codes providing a link. Data are anonymous. |
|  | Data collection forms INCLUDE IDENTIFIERS. The forms are locked in a secure cabinet or room with limited access by authorized individuals. Forms will be kept in study team’s possession during transport and will not be left unattended in a vehicle. When possible, de-identified copies will be used for coding and analysis. |
| X | Data collection forms ARE CODED with study participants’ random study ID numbers. Codes/links between study IDs and identifiers are stored securely in a separate place (locked storage cabinet or secure electronic database.) |
|  | Other: |
| 2. Electronic Data | |
| X | The data do not contain personally identifiable information |
| X | These data are stored on a secure server protected by limited access and strong password systems. Data are coded when possible. Portable electronic devices will not contain identifiable information unless encrypted. |
|  | Other: |
| 3. Other Identifiable Data Storage, Retention, and Destruction (Audiotapes, videotapes, photographs, etc.) will be retained and stored securely (locked in cabinet or room) until: | |
|  | Transcription is complete, then will be destroyed. |
| X | Analysis is complete, then will be destroyed. |
|  | Study is complete and file is closed. |
|  | Indefinitely. Provide justification for indefinite retention: |
| 4. Existing Biospecimens to be used in this study: N/A | |
|  | HAVE NO PERSONAL IDENTIFIERS. |
|  | INCLUDE IDENTIFIERS AND ARE CODED; the PI will not have access to the link or code connecting the identifiers to the specimens. |
|  | INCLUDE IDENTIFIERS, and the PI has access to those identifiers or to the link/code connecting specimens to individuals. The identifiers and/or code will be stored securely until the study is complete. |

B. Certificate of Confidentiality

Will the study data stored in the United States be protected by a Certificate of Confidentiality? If yes, explain who will apply for and maintain the Certificate. (<http://grants.nih.gov/grants/policy/coc/appl_extramural.htm>)

N/A

C. Data Security and Sharing

PIs have the responsibility for responsible stewardship of data and protecting data confidentiality. This responsibility includes protecting physical custody of the data, storage and sharing with appropriate data use agreements that contain the appropriate security provisions. Describe any additional plans beyond those identified in the table that you have for storing and sharing the study data and/or materials, and how responsibility for the data will be managed. Include the following details:

1. Where will the study data be stored?

2. Who controls access to the data?

3. Will data be shared only if de-identified?

4. What additional (if any) security controls will be in place?

The research team has two offices, one inside the camp and one in the nearby town of Kasulu. Data kept within the camp will be stored in a double-lock safe for a maximum of 48 hours. Within that 48 hour period the in-country project coordinator will transport data to the main office in Kasulu where the data will be stored in a locked cabinet. The only people with access to the safe are the in-country project coordinator and the one research assistant that has been elected as the lead research assistant by the research team. The in-country project coordinator is the only person with access to the data in Kasulu. The in-country project coordinator will permit access to the data assistant who is responsible for data entry and management. The data that is shared with the data assistant will be entirely de-identified and will be organized by an alphanumeric study identification code. There is a single Excel database that connects the study identification code with personal identifying information. This Excel database is controlled entirely by the team leader and no other personnel, besides study investigators if necessary, will have access to this information.

**VII. Risks of the Study**

1. Describe the risks, discomforts, and inconveniences associated with the study and its procedures, including physical, psychological, emotional, social, legal, or economic risks, and the risk of a breach of confidentiality. These risks should be described in the consent documents.

Risks related to participation in the study include discomfort discussing sensitive topics and safety of the participant. First, the research interviews as well as participation in the intervention require extensive and detailed discussion of sensitive topics including a detailed history of one’s experience with intimate partner violence, symptoms of psychological distress and other potentially traumatic events. Discussing these topics has the potential to make the participant uncomfortable or even, in some cases, result in re-experiencing traumatic events and related sequelae. However, it is our experience that most participants experience the ability to discuss materials related to (threats to) their wellbeing with well-trained research assistants as cathartic. In addition, the core of the Cognitive Processing Therapy component of the intervention is to manage these thoughts such that they can be reframed to avoid experiencing negative emotional reactions. Both the research and intervention team has been instructed on how to deal with participants that appear particularly distressed. In these cases, the in-country project coordinator will facilitate a referral to a gender-based violence protection worker or health provider whichever seems appropriate.

There are also safety risks related to participating in the study. There is the potential that someone (e.g. a husband/partner, family member) may find out that a woman is participating in the Nguvu intervention and furthermore that the Nguvu intervention is an intervention targeting women experiencing intimate partner violence in the past year. This might be aggravating to a husband/partner or other person that may have been the perpetrator of this violence or other community members that may see participating as disrespectful to the woman’s relationship. To minimize these risks we have designed the study in such a way that recruitment, interview and intervention sites are all in neutral locations that are common for women to frequent or in a private place where the woman feels comfortable – so that suspicion is not raised. Moreover, intervention facilitators and research assistants review participant’s safety during intervention sessions and research assessments respectively. We also provide both the intervention and control participants with a resource map/referral chart that includes contact information for agencies in case of emergencies as well as to receive other intimate partner violence response services – so that in effect, the study will increase safety and safety monitoring of respondents.

1. Describe the anticipated frequency and severity of the harms associated with the risks identified above; for example, if you are performing “x” test/assessment, or dispensing “y” drug, how often do you expect an “anticipated” adverse reaction to occur in a study participant, and how severe do you expect that reaction to be?

Slight discomfort discussing sensitive issues surrounding intimate partner violence and mental health may be common (e.g. 1 in 5 women), but we do not anticipate that this level of discomfort will get to a concerning level of distress for most women. In 1 out of 30 women, more serious psychological distress may be experienced that requires stopping the interview. As mentioned above, research assistants have been trained in responding to distress with empathetic reactions. With all women showing distress it will be reiterated that participants can choose not to answer any questions, take a break whenever they want, or stop the interview at any time. It is our experience that among women with whom an interview was stopped, most prefer to continue after a break and an opportunity to experience and explain their distress with research assistants. Issues surrounding safety compromised by participation are also expected to be infrequent. Women in Nyarugusu are generally actively involved in women’s groups and other activities and we do not believe that attending a meeting once per week (for the intervention group) and three research assessments will seem abnormal to family and community members.

1. Describe steps to be taken to minimize risks. Include a description of your efforts to arrange for care or referral for participants who may need it.

Participants that become highly distressed during research assessments will be referred to an International Rescue Committee (IRC) gender-based violence counselor and/or health provider at the Tanzania Red Cross hospital in the camp. In situations where suicidal ideation with a plan or serious intent is expressed, the research assistant and/or in-country project coordinator will accompany the participant to the hospital.

Our strategy to address the safety risk involves both prevention and screening. For prevention we will design the intervention and research assessment implementation in such a way that identifying the program as an intimate partner violence program is highly unlikely. We are implementing the intervention using existing International Rescue Committee staff. The International Rescue Committee is an international non-governmental organization providing community services to most, if not all, refugees in the camp. We also plan to hold intervention sessions and research assessments in spaces provided by the International Rescue Committee that are normally frequented by women for activities not necessarily related to gender-based violence (e.g. ‘empowerment’ activities, income generation activities, basic literacy training, women’s health issues, etc.). In regards to screening, the intervention facilitators will assess safety during each session. The research team also inquires about intimate partner violence and safety during their assessments. If there is reason to believe that the participant is at an elevated level of risk that requires immediate response, they will refer the participant to existing gender-based violence services, including the women’s shelters and other International Rescue Committee services in the camp according to existing SOPs.

1. Describe the research burden for participants, including time, inconvenience, out-of pocket costs, etc.

The research burden involves 3-4 assessments ranging from 30 minutes to 1.5 hours each. If the participant elects to complete the baseline assessment during the same visit as the screening, they will only have two assessments, which occur at baseline and 10 weeks after enrollment. If they prefer to conduct these interviews on separate occasions the baseline interview will take place within a week from the screening and will be followed by the post-intervention assessment. The only out-of-pocket expense relates to transportation. The camp is quite large and can take approximately one hour to travel by foot from Zone 7 (northwest) to Zone 1 (southeast). If transportation challenges would preclude participation or result in out-of-pocket expenses to a participant, the research team will provide transportation vouchers, but this is not expected to occur.

1. Describe how participant privacy will be protected during data collection if sensitive questions are included in interviews.

Besides the contact sheet completed during the screening process and the consent forms, none of the forms collected during interviews will contain the participant’s name or other contact information (besides a random alphanumeric identification code). This identification code will only be connected to the participant’s name in a single excel file that is password protected. Access to this file is restricted to the in-country project coordinator and the study investigators (if necessary). We plan to secure all data, even de-identified, in a safe in the camp or a locked cabinet in the Kasulu office.

**VIII. Direct Personal and Social Benefits**

1. Describe any potential direct benefits the study offers to participants (“payment” for participation is not a direct personal benefit).

Participating in the intervention is hypothesized to reduce psychological distress and intimate partner violence, which is a direct benefit to participants in the study. Furthermore, people in the treatment as usual condition will also receive a referral and resource list that will help them identify existing services they may benefit from in the camp. Additionally, it may also be therapeutic for the participants to discuss their experiences with the research team during the assessments in a private setting.

1. Describe potential societal benefits likely to derive from the research, including value of knowledge learned.

This is the first study to evaluate an integrated mental health and empowerment intervention for survivors of intimate partner violence in a refugee camp. If the intervention shows evidence of efficacy we have designed it such that it can be directly integrated into existing services for women in Nyarugusu refugee camp (i.e., training of nonspecialized community workers in a short intervention using a manual reflecting non-technical language). We have hired and trained staff working previously as gender-based violence counselors for the International Rescue Committee in attempt to promote sustainability and capacity in this setting. Furthermore, if efficacious this program could inform practices recommended by the UN Refugee Agency (UNHCR) and other agencies working with refugees for addressing intimate partner violence and psychological distress in refugees in other settings. However, given that this is not a wait-list controlled trial we cannot guarantee that participants in the control arm will receive the Nguvu intervention after the trial has been completed. A dissemination workshop has been planned upon completion of the trial to share results of the study with local and international partners with the purpose of discussing opportunities to improve the intervention and/or integrate it into existing practices. Sustainable implementation of the Nguvu intervention that would allow for control participants to receive the intervention will require additional funds, coordination and effort that we cannot guarantee through this research study.

**IX. Payment:**

1. Describe the form, amount, and schedule of payment to participants. Reimbursement for travel or other expenses is not “payment,” and if the study will reimburse, explain.

The participants will not receive any monetary payment for their participation in the study. The Tanzania national refugee policy specifically prohibits payment of refugees residing in Tanzania outside of small incentives. Thus we plan to provide participants with a small hygiene item (e.g. soap, toothbrush) at each of the three assessments. We will also provide a transportation voucher if distance to the intervention or assessment sites would preclude participation.

1. Include the possible total remuneration and any consequences for not completing all phases of the research.

There are no consequences for not completing all phases of the research. Since no monetary remuneration will be provided, this will not be affected by attrition or adherence to study procedures.

The co-investigators hold a monthly call and the individual teams have meetings/calls at least once per week related to the proposed study. Furthermore, there are also meetings across these teams. The MUHAS, IRC and UNHCR personnel meet every 2 weeks to coordinate activities. JHU, being the only entirely out of country partner, has personnel in the field at least half of the time and will have a representative in the field throughout the duration of the trial.

As shown in Figure 1, each organization (e.g. Johns Hopkins, MUHAS, IRC and UNHCR) is responsible for managing different components of the study. Johns Hopkins has been responsible for training the research and intervention field teams, developing the intervention, designing the pilot study and randomized controlled trial and coordinating all other study activities. MUHAS is the primary in-country research partner and is responsible for managing the research personnel and activities as well as intervention supervision. IRC is responsible for managing the intervention facilitators and supporting intervention activities by providing access to intervention space/offices and logistical support. UNHCR is responsible for facilitating and coordinating the relationships between Nguvu staff and other operations and agencies in Nyarugusu and ensuring that the project is aligning with the needs and priorities of the camp.

2. What are the qualifications of study personnel managing the project?

The principal investigator, [name], holds a PhD in public mental health and is an Assistant Professor in the Department of Mental Health at Johns Hopkins Bloomberg School of Public Health. Co-investigators from UNHCR ([name]) and MUHAS (Drs. [name] and [name]) hold MDs with specialization in psychiatry. [name] is the Senior Mental Health Officer at UNHCR and technically supports all UNHCR mental health activities globally. Drs. [name] and [name] are practicing psychiatrists and professors at Muhimbili University of Health and Allied Sciences/Muhimbili National Hospital. The co-investigator from the IRC is a licensed mental health counselor and currently serves as an international mental health technical advisor for the International Rescue Committee.

3. How will personnel involved with the data collection and analysis be trained in human subjects research protections? (Use the JHSPH Ethics Field Training Guide on our website.)

All members of the research team received 1.5 days of research ethics training adapted from the JHSPH Ethics Field Training Guide. They were also trained by a certified trainer in FHI research ethics training program. All other members of the research team have CITI training certification.

1. If the PI will not personally be on-site throughout the data collection process, provide details about PI site visits, the supervision over consent and data collection, and the communication plan between the PI and study team.

The principal investigator has previously made three site visits with plans for additional visits during the pilot and trial phases. [name] organizes a weekly field operations call with the in-country project coordinator ([name]), the research officer ([name]) and the MUHAS co-investigators (Drs. [name] and [name]).

B. Recordkeeping:

Describe how you plan to ensure that the study team follows the protocol and properly records and stores study data collection forms, IRB regulatory correspondence, and other study documentation. For assistance, contact [[contact]](mailto:[contact]).

The pilot phase will serve the dual purpose of testing implementation of the intervention and also research assessment procedures, including recordkeeping. The in-country project coordinator is responsible for collecting data collection forms from the double-lock safe located in the camp within 48 hours and the data assistant is then expected to enter the data within 72 hours from the time that the data arrives in Kasulu. During the pilot phase and the beginning of the trial, the in-country project coordinator will travel to the camp daily to hold end-of-day meetings with the research assistants to review the data that was collected during that day and identify any sources of confusion and/or error. The in-country project coordinator will be responsible to review all data collection forms prior to data entry (ideally at the end of each data collection day) to evaluate completeness and identify any errors as soon as possible. During the pilot phase the research officer will also enter data to compare with the data assistant and identify any inconsistencies in data entry.

C. Safety Monitoring

1. Describe how participant safety will be monitored as the study progresses, by whom, and how often. Will there be a medical monitor on site? If yes, who will serve in that role?

The Data Safety Monitoring Board (DSMB) will monitor participant safety regularly over the course of the study. As described below, the DSMB will be comprised of persons at the study site (Kasulu, Tanzania) as well as persons in Dar es Salaam, Tanzania and Baltimore, MD, USA and will communicate monthly via telephone/Skype. For urgent issues that occur between DSMB meetings, the in-country project coordinator, [name], will be responsible for reporting these incidents to study investigators [name], [name] and [name]. We have built in safety assessments throughout the research assessments and have also discussed the importance of evaluating safety in the intervention sessions. Thus, the research and facilitator teams will also be responsible for safety monitoring. For serious safety concerns, such as suicide, we have identified a counselor from the International Rescue Committee that has agreed to provide on-call services as needed. Unanticipated safety concerns will be reported to the in-country project coordinator and discussed immediately with co-investigators in Tanzania to determine an appropriate response.

2. If a Data Safety Monitoring Board (DSMB), or equivalent will be established, describe the following:

a. The DSMB membership, affiliation and expertise.

The DSMB will consist of 1 person from Johns Hopkins Bloomberg School of Public Health that is not affiliated with the Nguvu project, 2 persons from Muhimbili University of Health and Allied Sciences in Dar es Salaam Tanzania that are also unaffiliated with the Nguvu project and a representative from the International Rescue Committee in Kasulu, Tanzania. All DSMB members have experience and formal training in research methods and research ethics that will allow them to critically analyze all available data and determine whether participants are safe, protected and the trial should proceed.

b. The charge or charter to the DSMB.

The goal of the DSMB is to periodically review and evaluate the accumulated study data for participant safety, study conduct and progress, and, when appropriate, efficacy. The DSMB will make recommendations to the study management team concerning the continuation, modification or termination of the trial.

c. Plans for providing DSMB reports to the IRB.

The DSMB will meet monthly over Skype/telephone, but may be called together for urgent cases. During these meetings, the DSMB will review interim/cumulative data for evidence of study-related adverse events, evidence of efficacy according to pre-established statistical guidance (if appropriate), data quality, data completeness, data timeliness, adequacy of compliance with goals for recruitment and retention (including those related to the participation of women and minorities), adherence to the protocol, factors that might affect the study outcome or compromise the confidentiality of the trial data (e.g. protocol violations, unmasking), and factors external to the study that may impact participant safety or ethics of the study (e.g. scientific or therapeutic developments). A report summarizing their findings and discussion will be produced after each meeting. The DSMB will provide quarterly reports to the IRB summarizing results from the prior three meetings. This report will only be shared with the study investigators if the DSMB concludes that the trial must be halted. If the DSMB makes this determination they will share this information with the IRB immediately regardless of the reporting timeline.

3. Describe plans for interim analysis and stopping rules, if any.

Participant safety will be monitored throughout the study, both by the research team (during assessments) and intervention team (during each session of the intervention). The intervention program is specifically geared towards improving safety of women experiencing intimate partner violence. All study staff and members of partner organizations may note concerns regarding participant safety or other unanticipated problems and adverse events. Concerns can be expressed to the In-Country Program Manager, who will immediately notify an established DSMB. The DSMB will be formed by the In-Country Project Coordinator, a member of the GBV Working Group and the International Rescue Committee. The DSMB will review each case, and formulate recommendations that will be followed-up by the In-Country Project Coordinator. For medical issues, the DSMB will connect with co-investigator [name] (a licensed psychiatrist) and the clinical officer of the Tanzania Red Cross Society – as per existing referral pathways already described in the camp’s GBV SOPs. The DSMB will also determine whether a case forms a serious adverse event (i.e., unanticipated risks in which there is a threat of harm to participants or others, and that are related to the study), in which case the JHSPH and local IRBs (see below) will be notified.

D**.** Reporting unanticipated problems/adverse events (AE’s) to the IRB (***all studies must complete this section***):

Describe your plan for reporting to the IRB and (if applicable) to the sponsor. Include your plan for government-mandated reporting of abuse or illegal activity.

NOTE: The IRB does not require submission for all AEs, only those that are **unanticipated, pose risk of harm to participants or others, and are related to the study**.

Only adverse events that are determined to be serious adverse events (i.e., unanticipated risks in which there is a threat of harm to participants or others, and that are related to the study) by the DSMB will be notified to the JHSPH IRB and local IRBs.

E. Other IRBs/Ethics Review Boards:

If other IRBs will review the research, provide the name and contact information for each IRB/ethics review board and its Federal Wide Assurance, if it has one (available on OHRP’s website at <http://www.hhs.gov/ohrp/assurances>).

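### The protocol gives two irreconcilable DSMB memberships, one seating trial staff, and its SAE definition can leave out serious study-related harms that it foresees

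*Protocol*

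**What the plan says.** All the main text is in the Protocol's Safety Monitoring section and the adverse-event reporting section that follows it.

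- **Membership (item 2a).** "The DSMB will consist of 1 person from Johns Hopkins Bloomberg School of Public Health that is not affiliated with the Nguvu project". Two further seats go to "2 persons from Muhimbili University of Health and Allied Sciences in Dar es Salaam Tanzania that are also unaffiliated with the Nguvu project". IRC fills the fourth seat, with "a representative from the International Rescue Committee in Kasulu, Tanzania". Item 1 agrees, placing members in Kasulu, Dar es Salaam and Baltimore.
- **Reports (item 2c).** The board meets monthly, looks at study-related adverse events, data quality and, where appropriate, efficacy, and reports quarterly to the IRB. On confidentiality: "This report will only be shared with the study investigators if the DSMB concludes that the trial must be halted".
- **Interim analysis and stopping rules (item 3).** "The DSMB will be formed by the In-Country Project Coordinator, a member of the GBV Working Group and the International Rescue Committee". This board considers each case, must "formulate recommendations that will be followed-up by the In-Country Project Coordinator", and rules on whether a case is an SAE.
- **SAE definition (item 3, repeated in section D).** "unanticipated risks in which there is a threat of harm to participants or others, and that are related to the study". Section D sends only events that the DSMB places in this class to the JHSPH and local IRBs.
- **Foreseen harm (section VII).** If a partner learns that a woman is taking part in a programme on partner violence: "This might be aggravating to a husband/partner or other person that may have been the perpetrator of this violence".

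**The concern.** A DSMB needs one membership, and its members should not be judging their own work. Here a reader cannot tell which board decides whether the trial continues and which events reach the ethics committees. If item 3 prevails, one of the deciders is the person who helps to run the trial day to day.

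The SAE wording raises a second problem. Calling an event serious only if it was unanticipated and related confuses how bad an event is with whether it was expected and what caused it. In a trial of women with past-year partner violence, harm from a partner provoked by participation is among the most important risks, and it is one that the protocol itself foresees. The wording lets such an event fall outside the class that triggers individual notice to the IRBs.

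**Working it through.** No design figure is involved, so the check is a comparison of texts.

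**1. The two boards.**

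| | Item 2a | Item 3 |
|---|---|---|
| JHSPH | 1, unaffiliated | none |
| MUHAS | 2, unaffiliated | none |
| IRC | 1, affiliation not restricted | yes, affiliation not restricted |
| In-Country Project Coordinator | no | yes |
| GBV Working Group | no | 1 |
| Seats or parties | 1 + 2 + 1 = 4 | 3 |
| Expressly unaffiliated | 1 + 2 = 3 of 4 | 0 of 3 |

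The only party in common is IRC. Neither text is marked as replaced, and item 3 does not refer back to the membership in item 2a.

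**2. What the coordinator does elsewhere in the protocol.**

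- Section V.C.6.a: liaises with the intervention team so that sessions are scheduled for women in intervention clusters, and so knows allocation.
- Recordkeeping (section B): checks every form before data entry and, during the pilot and early trial, holds daily meetings with the research assistants, who are the blinded outcome assessors.
- Safety Monitoring item 1: reports urgent incidents that arise between meetings.
- Safety Monitoring item 3: carries forward the board's recommendations.

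A person with these duties who also sits on the board would classify events arising from operations that he or she helps to run, and would see interim data while in contact with blinded assessors. That sits badly with the halt-only rule on sharing reports in item 2c.

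**3. The IRC seat.** The study-management text makes IRC responsible for managing the intervention facilitators. Neither version requires IRC's DSMB member to come from outside that line.

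**4. Routing of incidents.** Item 1 has urgent issues go from the coordinator to study investigators. Item 3 has concerns go to an In-Country Program Manager, who notifies the DSMB at once. The recipient differs, and so does the title of the person reporting.

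**5. The SAE definition.** The conditions are joint: unanticipated, and a threat of harm, and related to the study. Take a partner's violent reaction on learning of participation. It is related to the study and harmful. Section VII foresees this kind of reaction, so it can be read as anticipated. The first condition then fails, the event is not an SAE however severe it is, and section D gives no event-level notice. The source of the wording is visible: the IRB's template note in section D lists the same three criteria as its threshold for submission, and the protocol has reused that threshold as its definition of serious.

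**The case against.** **The membership conflict may be loose drafting.** The verb in item 3 could mean that these parties convene the board, and the sentence before it speaks of a board already established. That is possible. But the sentence lists parties as a composition and then gives that body case review and SAE classification, so the natural reading is membership. Even on the convening reading, the text needs correcting.

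**A reader might infer that safety review is not independent.** That holds only if item 3 prevails. Under item 2a three of four members are unaffiliated, and the weak point there is the IRC seat alone.

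**A reader might infer that safety review is incomplete, or that harms could not be reported by arm.** Neither follows. The DSMB reviews study-related adverse events monthly, considers each reported case and reports quarterly to the IRB. Partner violence is a primary outcome in all women, research assessments in both arms ask about safety, and tabulation by arm may be left to a SAP that is not shown.

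**A reader might say that the coordinator's seat breaks the halt-only rule.** Not literally. That rule concerns study investigators, and section VII names the coordinator separately from them. It is a tension. The coordinator also knows allocation by design, so a seat would not newly reveal it.

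**A reader might use the protocol's 1 in 30 rate to count lost SAEs.** That rate is for distress that stops an interview, and most such women are said to prefer to continue after a break. It does not measure serious events.

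**A reader might infer inflated type I error from monthly efficacy review.** Item 2c ties any such review to statistical guidance set in advance, so the document does not support that inference.

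**The IRB notice threshold is the IRB's own, and the protocol does not define unanticipated.** Both are true. The definition therefore permits foreseen harms to be excluded; it does not exclude them in every case. The fault is using a submission filter to decide what counts as serious.

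**Conclusion.** The point holds on two counts.

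1. **DSMB membership is contradictory.** The two texts share only IRC, and expressly unaffiliated members go from three of four to none of three. Item 3, on its natural reading, places operational trial staff on the body that classifies SAEs. The routes for urgent incidents also conflict.
2. **The SAE definition is wrong in kind.** It has no seriousness criterion and requires the event to be unanticipated. A serious, study-related harm of a foreseen kind can therefore be left out of SAE classification and event-level IRB notice. The gap is confined to those two steps, because the DSMB still sees study-related adverse events.

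The first count assumes that item 3 describes composition. The second assumes that a harm of a kind described in section VII may be treated as anticipated. Neither affects the sample size or the primary analysis. What is at stake is the independence of oversight and the safety of participants.

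**What to change.** - Keep the membership in item 2a and delete the composition in item 3. The coordinator submits cases to the board but is not a member.
- Require IRC's member to come from outside the Nguvu intervention line.
- State one route for urgent incidents, with one named role reporting, and make items 1 and 3 agree.
- Define serious adverse events by their seriousness, whether or not they were expected. Keep the unanticipated-and-related test only as the filter for expedited IRB submission.

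The cost is mainly protocol wording, since the independent members are already planned. There will be somewhat more events to log, and because every participant has past-year partner violence, the increase could be noticeable. Partner violence captured as the primary outcome can be handled separately from event reports, which limits that burden.
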